### Effectiveness evaluation

The Healthy Working Approach will be evaluated in a randomised controlled trial with one year of follow-up, including four measurement moments in which the following primary and secondary outcomes will be measured.

### Outcomes

#### Primary outcome

*Need for Recovery* will be measured with the 11 dichotomous items (0 *no* or 1 *yes*) of the Questionnaire on Psychosocial Job Demands and Job Stress [38]. The need for recovery score is a percentage score (0 to 100) of positive answers on the items. Higher scores indicate a higher degree of need for recovery after work. The scale has shown to possess good psychometric qualities in terms of (content) validity and internal consistency (Cronbach’s alpha ranging from .83 to .92) [39].

#### Secondary outcomes

Within the intervention teams will uncover bottlenecks regarding their need for autonomy, competence and relatedness. We expect most of the bottlenecks to focus on reducing job demands and improving job resources, which benefit the satisfaction of the three needs at work and ultimately lessen the need for recovery. Therefore, the satisfaction of the needs for autonomy, competence and relatedness, as well as several psychosocial job factors were measured as secondary outcomes.

*Satisfaction of the needs for Autonomy, Competence and Relatedness* will be measured with 16 items of the validated Work-related Basic Need Satisfaction Scale on a 5-point scale (ranging from 1 *totally disagree* to 5 *totally agree*) [40]. Mean scores will be calculated for the subscales autonomy (6 items), competence (4 items) and relatedness (6 items). The Work-related Basic Need Satisfaction Scale is widely used and validated in the Dutch language [40]. The scales for autonomy, competence and relatedness satisfaction show good reliabilities with Cronbach’s alpha’s of on average .81, .85 and .82 respectively [40].

*Work engagement* will be measured with 9 items of the Utrecht Work Engagement Scale on a 7-point scale (ranging from 0 *never* to 6 *always)* [41]. Mean scores will be calculated for the subscales vigour (3 items), absorption (3 items) and dedication (3 items), as well as an average total score work engagement (9 items). The Utrecht Work Engagement Scale has shown good internal consistency and test-retest reliability. Across different nations the Cronbach’s alpha of the scale is satisfying with a value of .86 [41].

*Physical demands* will be measured with 3 items of the Netherlands Working Conditions Survey on a 3-point scale (ranging from 1 *no*, 2 *yes, sometimes* and 3 *yes, regularly)* [42]*.* With monitoring data of over 15 years, the Netherlands Working Conditions Survey is a well-known and used tool to assess working situations of Dutch employees [42]. For this study a mean score will be calculated, whereby a higher score means more physical demands (more pushing/pulling, repetitive movements and uncomfortable working postures).

*Quantitative job demands* will be measured with 3 items of the Netherlands Working Conditions Survey on a 4-point scale (ranging from 1 *never* to 4 *always)* [42]*.* A mean score will be calculated, whereby a higher score means a higher workload (working more quickly, having a lot of work and working extra hard). Cronbach’s Alpha of the scale is good with a value of .80 [42].

*Self-reported health* will be measured with the Dutch translation of 2 items from the third version of the Copenhagen Psychosocial Questionnaire [43, 44]. One item askes participants to rate their health either as *excellent* (100), *very good* (75), *good* (50), *fair* (25) or *poor* (0). The second item askes them to give points to their present state of health (0 for *worst* and 10 for *best conceivable state of health*). A higher scores on each item reflects a better general health. The Copenhagen Psychosocial Questionnaire is internationally widely used to study work characteristics and is recently well validated in Dutch [44, 45].

Several psychosocial work factors will also be measured with items from the Dutch translation from the third version of the Copenhagen Psychosocial Questionnaire [43, 44]. It concerns the core items for *influence at work* (1 item), *job satisfaction* (1 item), *possibilities for development* (2 items) and the long measurement of *social support from colleagues* (3 items). Answer categories of all factors range from 0 *rarely* to 100 *always*. Mean scores will be calculated in case of multiple items per subscale, whereby a higher score means more of the psychosocial work factor at hand. Previous research shows the items and scales of this questionnaire are reliable [44, 45].

#### Prognostic factors

At baseline, several prognostic factors will be included in the survey, namely: age, gender, educational level, job title, years employed and type of contract (temporary or permanent), number of contractual working hours, hours of informal care provision per week in the last six months and frequency and total number of working days of sickness absence in the last six months.

### Participant time line

Figure 1 shows an overview of the time line for participants in the intervention and waitlist control group. To promote participant retention and the completion of follow-up questionnaires, we will apply response-enhancing measures by offering teams that achieve a 75% response rate in the follow-up measurements a gift of their choice (e.g. fruit or flowers for the team).

**Fig. 1 Fig1:**
[figure not shown]
Timeline detailing the recruitment process, enrollment, randomization, and the different measurements and intervention meetings over time for participants of the Healthy Working Approach

### Sample size calculation

The primary outcome of this study is need for recovery [38], which we used for the calculation of the sample size. The mean need for recovery score of employees in occupational health services is 27.30 (SD = 29.75) on a scale of 0 to 100 [39]. The minimum relevant difference on the scale is 12 [46, 47]. An intraclass correlation (ICC) of 0.025 is assumed because previous studies have shown that ICCs at the workplace level for health-related outcomes are generally small [48–50]. Using the ICC for teams, a power of 80% and an alpha of 5%, the power analysis showed that a sample size of 161 employees will be needed to detect a difference of at least 12 points. Taking into account a 25% withdrawals and dropouts, the entire study population must consist of 202 long-term care workers (101 in intervention and 101 in control group).

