**Methods:**

We developed a participatory workplace intervention, the Healthy Working Approach. In this intervention teams will uncover what problems they face related to autonomy, relatedness and competence in their team, come up with solutions for those problems and evaluate the effects of these solutions. We will evaluate this intervention by means of a two-arm randomized controlled trial with a follow-up of one year. One arm includes the intervention group and one includes the waitlist control group, each consisting of about 100 participants. The primary outcome is need for recovery as proxy for sustainable employability. Intervention effects will be analysed by linear mixed model analyses. A process evaluation with key figures will provide insight into barriers and facilitators of the intervention implementation. The Ethical Committee Social Sciences of the Radboud University approved the study.

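### Under a two-sided 5% test, the stated 161 employees does not follow from the sample size paragraph's own inputs, and enrolling 202 does not leave 161 after 25% loss

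*Protocol article*

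**What the plan says.** All the inputs stand in the protocol article under Sample size calculation:

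- Variability: "The mean need for recovery score of employees in occupational health services is 27.30 (SD = 29.75) on a scale of 0 to 100".
- Target effect: "The minimum relevant difference on the scale is 12".
- Clustering: "An intraclass correlation (ICC) of 0.025 is assumed".
- Error rates: "Using the ICC for teams, a power of 80% and an alpha of 5" per cent. Sidedness is not given.
- Result: "the power analysis showed that a sample size of 161 employees will be needed to detect a difference of at least 12 points".
- Allowance for loss: "Taking into account a 25% withdrawals and dropouts", after which "the entire study population must consist of 202 long-term care workers (101 in intervention and 101 in control group".

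The abstract repeats the target as two arms, "each consisting of about 100 participants". The allocation section puts randomisation at team level, or at department level where teams work closely together. The analysis section plans a linear mixed model with a group-by-time interaction over the four measurements. The sample size paragraph mentions no correlation between measurements.

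**The concern.** The paragraph prints both its inputs and its output, so the output can be checked. A positive ICC can only raise the requirement above that of an individually randomised comparison. Yet 161 is below even the unclustered figure for a two-sided 5% test.

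This is the only power justification for the primary outcome. The Procedure section says recruitment runs until the target sample size is reached, so the figure sets the size of the trial. The step from 161 to 202 then loses more ground, because it does not preserve 161 after the stated loss.

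**Working it through.** **Inputs.** SD 29.75, difference 12, power 80%, alpha 5%, ICC 0.025, 25% loss and 1:1 allocation are all from the sample size paragraph. Respondents per team (m) is not stated, so values from 3 to 10 are assumed below.

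**1. The plan's own figures.** 161 x 1.25 = 201.25, which rounds up to 202. That step is reproduced. The 161 is not, as the next steps show.

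**2. Two-sided, no clustering.**
n per arm = 2 x (1.96 + 0.8416)² x (29.75/12)² = 96.5. The total is 193.0, or 194 as 97 per arm (196 with the t correction).
161/193.0 = 0.834, so 161 would need a design effect of 0.83. The design effect 1 + (m - 1) x 0.025 is never below 1 for m of 1 or more.

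**3. Two-sided, with clustering.**
- m = 5: design effect 1.10; 193.0 x 1.10 = 212.3, so 213.
- m = 10: design effect 1.225; 193.0 x 1.225 = 236.4, so 237.

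**4. Routes that do come near 161.**
- One-sided 5%, where 1.645 replaces 1.96: 76.0 per arm, 152 in total unclustered. With m = 3, 152 x 1.05 = 159.6 (160). With m = 4, 152 x 1.075 = 163.4 (164). With m = 5 it is already 168, and with m = 10 it is 187.
- Two-sided with baseline adjustment, variance factor 1 - r²: 161 is reached at r of about 0.41 unclustered, 0.49 at m = 5 and 0.56 at m = 10.
- Two-sided on the mean of three follow-ups, variance factor (1 + 2r)/3: 161 is reached if the correlation among them is at most about 0.75 unclustered, or 0.52 at m = 10.

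**5. Loss.** Keeping 161 after 25% loss needs 161/0.75 = 214.7, so 215. Enrolling 202 leaves 202 x 0.75 = 151.5, or about 75.75 per arm.

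**6. Simple two-sided comparison at about 151 evaluable.**
SE = 29.75 x √(2 x design effect/75.75); power = Φ(12/SE - 1.96); detectable difference at 80% power = 2.8016 x SE.

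| Respondents per team | Design effect | SE | Power | Detectable difference |
|---|---|---|---|---|
| no clustering | 1.000 | 4.83 | 70% | 13.5 |
| 5 | 1.100 | 5.07 | 66% | 14.2 |
| 10 | 1.225 | 5.35 | 61% | 15.0 |

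With 161 evaluable the corresponding powers are 72.5%, 68% and 64%. On the one-sided reading, power at about 151 is 78% with 3 per team and 77% with 4.

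**7. Baseline correlation that would restore 80% at about 151 evaluable.** Set 193.0 x (1 - r²) x design effect = 151.
- m = 5: 1 - r² = 151/212.3 = 0.711, so r is about 0.54.
- m = 10: 1 - r² = 151/236.4 = 0.639, so r is about 0.60.

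**The case against.** Three arguments can be made for the plan.

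**Sidedness is not stated.** With a one-sided 5% test, 161 exceeds the unclustered need of 152 and fits 3 to 4 respondents per team. This stands, in that the shortfall before clustering is a two-sided result. But nothing in the article announces a one-sided test, an unqualified 5% is conventionally two-sided, and even the one-sided reading falls short from 5 per team upwards.

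**The primary analysis is a mixed model over four measurements, not a comparison of two means.** This also stands. A reader might infer that the trial is underpowered, or that its true power is 61% to 70%. The document does not support that. The mixed model's power depends on correlations that are not given, and moderate ones could bring it to 80%. What can be said is that the paragraph claims no such credit, so its 161 is not derived from what it prints.

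**A journal article condenses the full protocol.** Leaving out team size, number of teams, formula or correlation is not in itself an error. The point here is the mismatch between printed inputs and printed output, and for a simple two-sided comparison no team size can remove it.

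**Conclusion.** The point holds for a two-sided 5% test of two means. The stated inputs need 194 employees unclustered, and about 213 or 237 with 5 or 10 respondents per team, against the stated 161. The 80% power is therefore not supported as written. It is not shown to be unattainable, since an unstated one-sided test with very few respondents per team, or an unstated correlation credit, could account for 161.

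The loss allowance is a separate arithmetic fault. Enrolling 202 leaves about 151 evaluable rather than 161, a shortfall of 13 enrolled against 215. Together, the two faults put a simple two-sided comparison at about 61% to 70% power, with a detectable difference of 13.5 to 15.0 points against the protocol's own minimum relevant difference of 12.

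These sizes rest on assumed team sizes, equal clusters, a normal approximation, and counting the whole 25% as lost information.

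**What to change.** Correct the sample size paragraph to report what was actually calculated: sidedness, respondents per team, design effect and any correlation used. Show the loss allowance as a division by 0.75, or state that about 151 evaluable are expected from 202. Then do one of the following.

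- **(a) Restate the power.** For a simple two-sided comparison at about 151 evaluable, give about 70% unclustered, 66% at 5 per team and 61% at 10 per team, with the detectable differences shown above.
- **(b) Justify the size through the baseline score.** State the assumed baseline-to-follow-up correlation (about 0.54 at 5 per team or 0.60 at 10 per team for 151 evaluable) and make the matching baseline-adjusted analysis primary. Unless this was the calculation made at the time, label it as made after data collection began, which the Study Design section dates to May 2021.

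The cost is one rewritten paragraph and, under (b), a matching line in the analysis section. Neither option needs extra enrolment. The downside is a less favourable stated power, or one that depends on an explicit assumption.

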### Procedure

Long-term care organisations are invited to participate in the study. After permission has been obtained, care teams are invited to participate via internal communication tools (e.g., intranet), and a personal e-mail with a link to the baseline questionnaire (T0). The questionnaire starts with an eligibility check followed by a digital informed consent. After participants have given their consent and their contact details, they are redirected to the main questionnaire. Information and questionnaires are also available in print. To enhance the response rate, the researcher will contact the teams to ask them how the research team can support them in filling out the questionnaires, for example by visiting with a laptop, or by bringing over hardcopy questionnaires. Recruitment of participants will continue until target sample size is reached.

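### The target of 202 adds 25% to 161 instead of allowing for a 25% loss, so it covers about 20% dropout and leaves about 151 completers if 25% drop out

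*Protocol article*

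**What the plan says.** All the figures stand in the protocol article under *Sample size calculation*. With a smallest relevant difference of 12 points on the need for recovery scale, and "Using the ICC for teams, a power of 80% and an alpha of 5" per cent, "the power analysis showed that a sample size of 161 employees will be needed to detect a difference of at least 12 points". The next sentence gives the allowance for attrition: "Taking into account a 25% withdrawals and dropouts, the entire study population must consist of 202 long-term care workers", split as "101 in intervention and 101 in control group".

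Under *Procedure* the article adds: "Recruitment of participants will continue until target sample size is reached". The only enrolment target in the article is 202. The abstract's approximate figure of 100 per arm agrees with it, so 202 does not look like a misprint. No other section gives a different dropout rate or another way of allowing for dropout.

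**The concern.** A dropout rate is a share of those enrolled. To keep n workers after losing a fraction d, one must enrol n/(1 − d). Multiplying by (1 + d) gives a smaller number, and the gap grows with d. At 25% it is no longer a matter of rounding.

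The three printed figures (161 needed, 25% lost, 202 enrolled) therefore cannot all hold. What is at stake is whether the enrolment target delivers the stated 80% power on the primary outcome under the protocol's own attrition assumption.

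**Working it through.** **Inputs**, all from *Sample size calculation*: required number 161; dropout 25%; enrolment target 202 (101 per arm); power 80%; alpha 5%, with sidedness not stated.

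**1. Reproduce the printed target.** The article does not print its formula, so both candidates were tried.

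- n × (1 + d) = 161 × 1.25 = 201.25, rounded up to 202. This matches exactly and splits into 101 + 101.
- n / (1 − d) = 161 / 0.75 = 214.67, rounded up to 215. This does not match; it is 13 above 202.

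**2. Check the target without assuming any formula.**

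- Left after 25% loss: 202 × 0.75 = 151.5, that is, 151 to 152.
- Shortfall: 161 − 151.5 = 9.5 workers, or 9.5/161 = 5.9%.
- Loss that 202 can absorb: 1 − 161/202 = 20.3%. Equivalently, 161/0.80 = 201.25.

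**3. Target that meets the stated assumption.** 215 in total, or 216 (108 per arm) for equal arms. Check: 216 × 0.75 = 162, which is at least 161. This is 14 more than 202.

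**4. Effect on power, on the trial's own terms.** Take 161 as giving exactly 80%, as the article says, and scale by the number analysed:

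power(n) = Φ[(z_α + z_0.80) × √(n/161) − z_α]

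Two-sided 5%: z_α = 1.960, z_0.80 = 0.842, sum 2.802. For n = 151.5, √(151.5/161) = 0.970, so 2.802 × 0.970 − 1.960 ≈ 0.758 and Φ(0.758) ≈ 77.6%.

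| Completers | Two-sided 5% | One-sided 5% |
|---|---|---|
| 151 | 77.4% | 77.7% |
| 151.5 | 77.6% | 77.9% |
| 152 | 77.7% | 78.0% |
| 161 (reference) | 80.0% | 80.0% |

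The loss is about 2 to 3 percentage points, whichever sidedness was meant. The scaling holds the design effect fixed. If dropout thins teams without removing whole teams, the design effect falls a little and the loss is slightly smaller.

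**The case against.** **The analysis can use incomplete records.** *Data management and analysis* plans intention-to-treat linear mixed models and imputation, and there are three follow-up measurements. A worker who leaves after the 6- or 9-month questionnaire still contributes data. This stands in part: 151 counts completers, and the practical loss of power may be smaller than computed. It does not reconcile the figures, because the sample size section treats the 25% as a loss to be made up by recruitment and takes no credit for partial data.

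**The final count may not be exactly 202.** Teams enter as units, need a minimum response and are randomised in pairs, so enrolment may overshoot. The recruitment sentence also speaks of a target without giving its number. A reader might infer that recruitment is bound to stop too early. The documents support only that the stated target is too low for the stated dropout, not that the achieved number will be.

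**A larger loss of power.** A reader might apply the printed SD of 29.75 and the 12-point difference in a simple two-sided comparison and report power falling from 72.5% to 69.9%, or from 63.8% to 61.1% with 10 workers per team. Those figures do not measure this error. Their starting values already contain a different question, how 161 was obtained. The article states neither the sidedness nor the method behind 161, and a team size of 10 appears nowhere in it. Even in those figures, the drop due to the dropout step is again only 2 to 3 points.

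**The formula is inferred.** This is true, but the check in step 2 needs no formula: 25% off 202 is not 161.

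**Conclusion.** The point holds as a definite but modest arithmetic inconsistency. Under the protocol's own 25% assumption, the target of 202 yields about 151 completers, 9 to 10 below the stated requirement, and it covers only about 20% loss. Power is then about 77.5% against the stated 80%.

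This rests on two assumptions: that 161 gives 80% power, as the article says, and that the 25% lost contribute nothing. The second makes 77.5% a cautious figure. The slip does not threaten the trial's validity. It needs correcting because a stated target does not deliver the stated power. Whether 161 follows from its own inputs is a separate matter, and this conclusion does not depend on it.

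**What to change.** Correct the dropout sentence in *Sample size calculation* in one of two ways.

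1. Keep 202 and say what it supports: either that it tolerates about 20% dropout, or that 25% dropout leaves about 151 completers with power of about 77.5% on the trial's own basis (two-sided). The cost is one sentence and a slightly less favourable figure. No one more need be recruited.
2. If recruitment is still open and the sponsor chooses, restate the target as 216 (108 + 108), from 161/(1 − 0.25). This is not merely an edit: it means 14 more workers, possibly a further pair of teams, in a trial that has been collecting data since May 2021.

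The first is enough to make the figures agree.

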### Data management and analysis

Before the start of the project, all issues of data management will be addressed in a data management plan. For this, Radboud University has a tool, that includes feedback from Research Data Management (RDM) Support. Training and support in writing a data management plan are offered by the section RDM Support and the data steward of the institute. In order to check whether the research has been carried out properly and reliably, authorised persons within the Behavioural Science Institute or Radboud University and (inter)national supervisory authorities (for example, the Netherlands Authority for the Protection of Personal Data) are able to inspect the data. While research is ongoing, data will be stored on the Radboud University’s network. The server space allows for managed access to and the sharing of data between and among partners and guests during the project. Safe and secure storage of data is guaranteed by the Information Technology security and safety protocols of the campus network.

We will perform descriptive analyses (means, standard deviation, frequencies) on all outcomes and covariates. For the main analysis, we will perform linear mixed model analyses with need for recovery as primary outcome, and group (intervention/control) x time interaction as independent variable, taking into account potential confounding prognostic factors. Potential confounders are included in the model when they account for at least 10% change in the main effect size of the group x time interaction. We will take into account nesting of the data. Similar analyses will be done with the secondary outcome measures.

Main analyses are performed according to the “intention to treat” principle and the unit of analysis is on the individual level. In addition, we will perform a per-protocol analysis to take into account teams in the intervention group that did not participate in the intervention or did not implement the intervention as planned. Any cases of missing data will be dealt with by imputation.

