## Methods

### Study Design

This is a randomised controlled trial with an intervention group and waitlist control group. There will be four measurement moments: at baseline (T0), 6 months (T6), 9 months (T9) and 12 months after baseline (T12). Data collection started in May 2021. The study protocol was approved by the Ethical Committee Social Sciences of the Radboud University (number: ECSW-2021-012).

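### The primary group x time contrast is left without stated baseline adjustment; a common T0 mean or T0 as a covariate would be more precise at no cost, by an amount that depends on an unstated correlation

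*Protocol article*

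**What the plan says.** The section on data management and analysis plans a linear mixed model for need for recovery, with the "group (intervention/control) x time interaction as independent variable, taking into account potential confounding prognostic factors". Covariates have one route into the model, a change-in-estimate rule applied to the interaction: "Potential confounders are included in the model when they account for at least 10% change in the main effect size of the group x time". The section also says that nesting will be taken into account and that the secondary outcomes will be analysed similarly.

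The study design section counts baseline among the repeated measurements: "at baseline (T0), 6 months (T6), 9 months (T9) and 12 months after baseline (T12"). The candidate covariates, under Prognostic factors, are personal and job characteristics, starting with "age, gender, educational level, job title, years employed and type of contract (temporary or permanent), number of contractual working hours", followed by informal care and sickness absence. Baseline need for recovery is not among them, and no other section names it as a covariate. The article does not say whether a group main effect is fitted, that is, whether the groups may differ at T0 or share one T0 mean.

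**The concern.** With T0 as an outcome wave and the usual group main effect, each group x time coefficient compares the groups on change since T0. That contrast subtracts the whole baseline value, noise included. A baseline-adjusted comparison subtracts only the part that predicts follow-up, so it is more precise at any baseline to follow-up correlation below 1. When the correlation is modest, subtracting baseline adds more noise than it removes.

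What is at stake is power for the primary outcome, and for every secondary outcome analysed in the same way. Baseline need for recovery is already collected. Teams enter the study only after enough members have completed the T0 questionnaire, so it appears to be collected before allocation. The more precise analysis therefore needs no extra data.

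**Working it through.** **Inputs from the article.** SD 29.75 ("The mean need for recovery score of employees in occupational health services is 27.30 (SD = 29.75"); target difference 12 points ("The minimum relevant difference on the scale is 12"); ICC 0.025; 161 employees before dropout; alpha 5%; power 80%.

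**Assumed, because not stated.** Correlation rho between need for recovery at T0 and at follow-up, shown over a range and taken as equal between all waves; two-sided test; 8 analysed members per team for the power illustration.

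**The plan's own figure.** The article gives no precision figure for this contrast. Its related figure is 161. From the stated SD and difference, two-sided, n per arm = 2 x 29.75^2 x (1.960 + 0.842)^2 / 12^2 = 96.5, so 97 per arm or 194 in total before clustering. The 161 is thus not reproduced. That is a separate matter, and 161 is used below only as the number analysed. The calculation uses a single-time SD and no rho, so it matches the change contrast only where 2(1 - rho) = 1, that is, at rho = 0.5.

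**Variance per arm at one follow-up, in units of SD^2/n.**
- Ignoring baseline: 1
- Change from baseline (free group effect at T0): 2(1 - rho)
- Baseline-adjusted (common T0 mean, or T0 as covariate): 1 - rho^2
- Ratio adjusted/change: (1 - rho)(1 + rho) / [2(1 - rho)] = (1 + rho)/2

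| rho | change | adjusted | ratio | variance reduction | SE reduction |
|---|---|---|---|---|---|
| 0.2 | 1.60 | 0.96 | 0.60 | 40% | 23% |
| 0.4 | 1.20 | 0.84 | 0.70 | 30% | 16% |
| 0.5 | 1.00 | 0.75 | 0.75 | 25% | 13% |
| 0.6 | 0.80 | 0.64 | 0.80 | 20% | 11% |
| 0.7 | 0.60 | 0.51 | 0.85 | 15% | 8% |
| 0.9 | 0.20 | 0.19 | 0.95 | 5% | 3% |

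Below rho 0.5 the change column exceeds 1, so the change contrast is less precise than a comparison that ignores baseline.

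**Average of T6, T9 and T12.** Change: (1 + 2rho)/3 + 1 - 2rho = 4(1 - rho)/3. Adjusted: (1 + 2rho)/3 - rho^2 = (1 - rho)(1 + 3rho)/3. Ratio: (1 + 3rho)/4, which is 0.55 at rho 0.4 and 0.775 at rho 0.7, a variance reduction of 45% to 22.5%.

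**Power illustration at T12.** Design effect 1 + 7 x 0.025 = 1.175, applied equally to both contrasts; 80.5 per arm. SE = 29.75 x sqrt(2 x f x 1.175 / 80.5), with f from the table. At rho 0.4 this is 5.57 (change) against 4.66 (adjusted).

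| rho | power, change | power, adjusted |
|---|---|---|
| 0.4 | 58% | 73% |
| 0.5 | 66% | 78% |
| 0.6 | 75% | 84% |
| 0.7 | 86% | 91% |

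These use a normal approximation, so the levels are optimistic if teams are few; the gap between the columns is what matters here.

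**Check with explicit team components.** A generalised least squares calculation over four waves, with 10 per team and half of the team variance persistent (both assumed), gives T12 standard errors of 5.60 against 4.71 (rho 0.4), 5.19 against 4.49 (0.5), 4.75 against 4.22 (0.6) and 4.26 against 3.88 (0.7). These are reductions of 16%, 13%, 11% and 9%, in line with the simple formula.

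**The case against.** The strongest reply is that the article never mentions a group main effect. It names only the interaction. A model with a common T0 mean and group x follow-up terms fits that wording, and it would lose nothing. Such parameterisation is often settled in an analysis plan, which is not shown. The absence of need for recovery from the prognostic factors also proves little, since in a model with T0 among the outcomes it belongs on the outcome side. And an unconstrained group x time model is a standard, valid analysis of a randomised trial.

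Much of this stands. A reader might infer that the plan never uses baseline need for recovery. It does: T0 is the reference of the contrast. A reader might also suppose that only T6 to T12 are outcomes, so that the interaction would miss an effect that is present at T6 and sustained. The article does not support this, because it counts T0 among the four moments at which the outcomes are measured. Nor does the contrast bias the result. Under randomisation, chance imbalance at T0 averages out, and its cost is already in the variance.

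What does not stand is that this is only missing detail. The article does fix the effect parameter and the route for covariates, and its conventional reading is the less precise contrast. A better one is available from the same data.

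**Conclusion.** The point holds as a free improvement to the primary analysis, not as an error that invalidates it. If a group main effect is fitted, the planned contrast has 2/(1 + rho) times the variance of a baseline-adjusted one.

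A reader might infer a definite loss of 15% to 30%. The documents do not support a fixed figure: it rests on an assumed rho of 0.4 to 0.7, a single follow-up and the variance scale. On the standard error scale the same range is about 16% to 8%, and the variance reduction runs from 40% to 5% for rho from 0.2 to 0.9. The power figures also assume 8 members per team, 161 analysed and a two-sided test. The algebra is certain; the size is not, and it is zero if a common T0 mean is already intended.

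**What to change.** State one of two forms of the linear mixed model:

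1. Keep T0, T6, T9 and T12 as outcomes and constrain the groups to a common T0 mean: no group main effect, group x follow-up terms kept.
2. Take T6, T9 and T12 as outcomes and T0 need for recovery as a prespecified covariate, exempt from the 10% change rule. Report the group effect at follow-up. Under this form the interaction must not remain the test, because it would be near zero for an effect that is constant from T6 on.

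Use the same form for each secondary outcome with its own baseline value, and confirm that T0 is completed before allocation is known. If the first form is already intended, one sentence saying so settles the point. The cost is model wording only; no new data are needed.
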